Demonstrate non-inferiority of a stepped-care model of DP after short IP stabilisation versus full-time IP based on BMI at 12 months post-randomisation (primary outcome).Demonstrate non-inferiority of a stepped-care model of DP after short IP stabilisation in term of clinical, biological outcomes, AN symptoms, comorbidities, and relapse at different time points (weight normalization, 6, 12 months).Assess the impact of a stepped-care model of DP after short IP stabilisation versus full-time IP on treatment satisfaction and quality of life of patients and parents at 6 and 12 months.Assess the impact of the prospect of discharge to DP on initial IP (duration before somatic stabilisation, motivation to change) at inclusion and somatic stabilisation.Determine factors associated with positive response to stepped-care model of DP after short IP.Determine the cost-utility and cost-effectiveness of a stepped-care model of DP after short IP stabilisation compared with full-time IP.

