### Measures (Table 1)

**Table 1 Tab1:** Overview of measures and time of assessment

Assessment	Inclusion	Stabilisation	Weight normalization	6 months	12 months
*Clinical assessment weight, height, BMI *	x	x	x	x	x
tanner stage	x			x	x
*Nutritional markers* prealbumin, leptin, total ghrelin and IGF1	x		x		x
*Radiology* Bone mineralization (dual-energy X-ray absorptiometry) Bone maturation (en face radiograph of the left wrist)	x				x
*Global psychosocial* CGI	x		x	x	x
*Eating symptomatology* EDI-c, MRS	x		x	x	x
*Anxiety and depressive symptomatology* CDI, STAIC	x		x	x	x
*Self-esteem Scale* Rosenberg	x		x	x	x
*Motivation to change* HAQ-11S, Motivation questionnaire	x		x	x	x
*Treatment acceptability and quality of life* CSQ-8, SF-12	x		x	x	x
Resource consumption		x	x	x	x

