#### Secondary outcomes

*Biological and radiological outcomes* will be collected. *Nutritional status* will be assessed with prealbumin, leptin, total ghrelin and IGF1. Body composition and *bone mineralisation* will be estimated by using dual-energy X-ray absorptiometry (DEXA, GE Lunar ProdigyCorp., Madison. WI). Bone mineral measurements will be expressed as standard deviation score according to age and sex (SDS). *Bone maturation* will be assessed from an en face radiograph of the left wrist, interpreted using the Greulich and Pyle atlas.

*Global clinical and psychological evaluation* will be assessed with the *Clinical Global Impression* (CGI) [20] scale. CGI is scored on a two-part 7 response levels evaluating illness severity (CGI-S) and improvement (CGI-I) from 1 (“not ill”/ “very much improved”) to 7 (“extremely ill”/ “much worse”).

*Eating disorder symptomatology* will be assessed with the *Morgan and Russell scale* (MRS) [21] and the *Children Eating Disorders Inventory* (EDI-c) [22, 23]. The MRS is a questionnaire designed to evaluate the long-term evolution of the eating disorder and is used to assess the main aspects of anorexia nervosa over a six-month period. A version has been adapted for younger children, with deletion of non-appropriated items as "menstruation", "psychosexual functioning" and "emancipation". The assessment of the adapted procedure has 8 subscales divided into 3 groups: Eating; Mental status; Socioeconomic Status.

The EDI-c is adapted form of the EDI for children from 8 years of age onwards [22, 23]. This is a multidimensional self-questionnaire that assesses different psychological, behavioural and emotional characteristics associated with eating disorder symptoms. It comprises 91 items divided into 11 factors: Drive for Thinness, Bulimia, Body Dissatisfaction, Low Self-Esteem, Personal Alienation, Interpersonal Insecurity, Interpersonal Alienation, Interoceptive Deficits, Emotional Dysregulation, Perfectionism, Asceticism, and Maturity Fears. Each of the 91 items is rated from 'never' to 'always', respectively from 0 to 3 for direct items and from 3 to 0 for indirect items.

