### Data analysis

#### Sample size

We calculated the sample size for a one-sided Student’s t test with a significance level of 2.5% and a power of 90% based on the clinically determined non-inferiority margin for a difference in BMI of 1 kg/m2, assuming a distribution of the BMI of 16,6 ± 1,35 kg/m^2^. This procedure led to a required sample size of 80 patients (40 per group). Assuming a dropout rate of 10% [8], we calculated a sample size of 88 patients. We aim to include 88 children with EOAN (44 per group).

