#### Statistical analysis plan

The statistical analysis of the data will be performed using an intention-to-treat analysis, all patients allocated to the control group or experimental group will be analysed. The descriptive analysis for each group at each assessment time will be expressed as number (percentage) for categorical variables, and as mean (SD) or Median [IQR] according to their normal or non-normal distribution for quantitative variables. As described above, the primary outcome for non-inferiority analysis is based on the comparison of the BMI at 1 year after inclusion between the two groups with a two-sided 95% confidence interval. Experimental strategy will be considered as non-inferior if the confidence interval upper limit of the difference in BMI between the 2 groups is less than 1 kg/m^2^ (non-inferiority margin) with a 0.025 alpha risk. The comparative analysis between the 2 groups for the primary or secondary criteria will be carried out using the appropriate tests: Chi^2^ test or Fisher's exact test for qualitative variables; Student's t test or non-parametric Wilcoxon test for quantitative variables, according to their normal or non-normal distribution. To determine prognosis factors associated with positive response to stepped-care model of DP after short IP, a regression model will be used to search for factors associated with the effect of the intervention, integrating the MRS score as the explained variable, and the CGI score, the HAQ11 and motivation questionnaire scores, and the severity of the weight deficit as explanatory variables.

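### The regression for factors of positive response models the MRS score without the inclusion MRS score the trial collects, so factors that merely track initial severity can appear as response factors

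*Protocol article*

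**What the plan says.** The fifth objective in the Background is to "Determine factors associated with positive response to stepped-care model of DP after short IP". The Statistical analysis plan section gives the matching analysis the same purpose, "To determine prognosis factors associated with positive response to stepped-care model of DP after short IP", and adds that the regression searches for factors linked to the intervention's effect. The model is then spelled out as "integrating the MRS score as the explained variable, and the CGI score, the HAQ11 and motivation questionnaire scores, and the severity of the weight deficit", the last four being the explanatory variables.

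Two other places bear on this. Under Secondary outcomes, the MRS is a status measure that "is used to assess the main aspects of anorexia nervosa over a six-month period". In Table 1 the row reads "Eating symptomatology* EDI-c, MRS x x x x": the MRS is scheduled at inclusion, weight normalisation, 6 months and 12 months. A starting value is therefore planned for every child, but the regression does not use it.

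The section does not name the visit for the MRS outcome or for the explanatory scores. It also does not say which part of the CGI (severity or improvement) is meant.

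**The concern.** The aim is worded as response and as effect of the intervention. The outcome is worded as a score, not a change, and nothing in the model represents where the child started on that score. A model of later status without starting status cannot separate a child who improved less from a child who began worse.

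The listed factors make this more than a formality. CGI severity and weight deficit measure how ill the child is, and alliance and motivation may also go with severity. Any of them that correlates with inclusion MRS can pick up its association with later MRS.

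What is at stake is the reading of the fifth objective. A result such as worse CGI predicting poorer response to stepped care could be used in deciding who is offered day care, when the data might show only that children who start worse also end worse.

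**Working it through.** **The plan's own figure.** The regression has no stated sample size or power. The only stated figure is the size for the primary outcome: a "one-sided Student’s t test with a significance level of 2.5% and a power of 90"%, with a "non-inferiority margin for a difference in BMI of 1 kg/m2" and an SD of 1.35. The exact non-central t calculation gives 89.8% power at 39 per arm and 90.5% at 40, so 40 per group (80 in all) reproduces. It is used here only to set n: 40 for one arm, 80 for both.

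**Assumptions (none is in the document).**
- B is inclusion MRS, standardised. Follow-up MRS is Y = ρB + noise with unit variance, and ρ = 0.5.
- Each of the four factors is X = rB + independent noise with unit variance, and r = 0.3, 0.5 or 0.7.
- Given B, no factor has any relation to Y, so every significant factor is a false flag.
- Factors are measured at inclusion. Tests are two-sided at 5%.

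**Formulae without B in the model.** Two factors correlate r² with each other, and each correlates ρr with Y. Then:
- coefficient per factor: β = ρr / (1 + 3r²)
- variance explained: R² = 4ρrβ
- variance inflation: V = (1 + 2r²) / [(1 − r²)(1 + 3r²)]
- non-centrality of the t statistic: δ ≈ β / √[(1 − R²)V / (n − 4)], on n − 5 degrees of freedom

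**One case in full, r = 0.5 and n = 80.** β = 0.25/1.75 = 0.143. R² = 4 × 0.25 × 0.143 = 0.143. V = 1.5/(0.75 × 1.75) = 1.143. δ = 0.143/√(0.857 × 1.143/76) = 1.26. With 75 degrees of freedom the chance of p < 0.05 is 23.7%.

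**All cases** (formula; simulation of the same set-up, 20,000 trials per row, agrees within about 0.3 percentage points; the last two columns are from simulation):

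| n | r | β | δ | each factor flagged, B omitted | at least one of four, B omitted | at least one of four, B included |
|---|---|---|---|---|---|---|
| 40 | 0.3 | 0.118 | 0.73 | 10.9% | 37% | 18% |
| 40 | 0.5 | 0.143 | 0.87 | 13.4% | 46% | 18% |
| 40 | 0.7 | 0.142 | 0.76 | 11.4% | 40% | 18% |
| 80 | 0.3 | 0.118 | 1.06 | 18.1% | 56% | 18% |
| 80 | 0.5 | 0.143 | 1.26 | 23.7% | 70% | 18% |
| 80 | 0.7 | 0.142 | 1.10 | 19.2% | 64% | 18% |

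With B in the model each factor is flagged in about 5% of trials in every row. The 18% in the last column is what four tests at 5% give anyway: 1 − 0.95⁴ = 18.5%.

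**Sensitivity.**
- r = 0: about 5% per factor with or without B, so no inflation.
- ρ between 0.3 and 0.7, with r of 0.3 or 0.5: 7–25% per factor at n = 40 and 9–48% at n = 80 without B.
- Only one factor correlated with B and the other three unrelated to severity (ρ = 0.5): that factor is flagged in about 14%, 32% and 58% of trials at n = 40 for r = 0.3, 0.5 and 0.7, and in 25%, 60% and 89% at n = 80.
- Inclusion MRS measured with an assumed reliability of 0.7, n = 80, all four factors correlated: the adjusted model still flags each factor in about 7%, 9% and 11% of trials.

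**The case against.** The strongest reply is that the article does not define response as improvement from entry. It speaks of prognosis factors. If response means reaching a good MRS state, a child who starts worse and ends worse is a real prognostic association and not a false one. That is fair as far as the single word goes. The same sentence, however, ties the factors to positive response and to the intervention's effect, and a status-only model delivers neither.

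A second reply is that visits and scoring are details for the full protocol or the SAP. That holds for the missing visits, which are not criticised as omissions here. It does not hold for the covariates: the article names the outcome and lists the explanatory variables, and inclusion MRS is not among them. The figures above do depend on reading the outcome as a follow-up level and the factors as inclusion values.

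A third reply is that CGI and weight deficit already carry part of the initial severity. This stands, and it limits the size. A reader might infer that spurious factors are bound to be reported, or that error rates of 60–90% are to be expected. The document supports neither. It gives no correlations, there is no inflation when the factors are unrelated to inclusion MRS, and the very high rates arise only if one factor alone carries baseline severity.

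Two limits of the remedy also stand. The return to 5% assumes an inclusion MRS free of measurement error. And the listed model has no arm or arm-by-factor term, so adding inclusion MRS does not show whose treatment effect differs.

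**Conclusion.** The point holds in a conditional form. As listed, the regression can present markers of initial severity as factors of positive response, because it leaves out the inclusion value of its own outcome. Under the stated correlations the false-flag rate per factor is roughly two to five times the nominal 5%: 11–13% with one arm and 18–24% with both. These are illustrations under assumed correlations, not predictions for this trial. The analysis is secondary and exploratory, and the BMI non-inferiority comparison does not depend on it. It is worth correcting because the result could be read as guidance on who benefits from day care.

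**What to change.** Add the inclusion MRS score as a fixed covariate, so that follow-up MRS is modelled conditional on inclusion MRS. In the same sentence name the MRS visit used as outcome, state that the explanatory scores are inclusion values, and say which CGI part is used. Interpret the other factors conditional on inclusion MRS, and note that measurement error in the MRS may leave some residual confounding. Do not describe the results as modifiers of the treatment effect on the strength of this change alone.

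The cost is one degree of freedom and a line of wording. No new data are needed, since Table 1 already schedules the MRS at inclusion.

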#### Economic evaluation

A cost-utility (CUA) and cost-effectiveness (CEA) analyses will be carried out from the all-payers perspective (including statutory health insurance, complementary health insurances and patients’ out-of-pocket expenditures). In a secondary analysis, a societal perspective will be adopted to account for productivity losses in both treatment arms. The time horizon will be that of the follow-up (12 months) and as such in accordance with French guidelines, no discounting rate will be applied to costs and effectiveness [31].

The effectiveness criteria will be quality-adjusted life-years (QALYs) in the CUA and BMI in the CEA. QALY will be derived from patients’ responses to the SF-12 at inclusion, weight normalisation, 6 and 12 months. In the absence of a French utility value set for the SF-12, the British set will be used.

Only direct costs related to the pathology and incurred between inclusion and 12 months will be included in the main analysis (IP and DP, ambulatory consultations, complementary examinations, medical transport…). In the secondary analysis from the societal perspective, indirect costs due to parents’ productivity loss related to the pathology of their child will also be included. Data sources for costs will include questionnaires and the centre’s discharge database, which records all admissions (IP and DP).

Incremental cost-effectiveness ratios will be calculated by dividing the difference in mean costs in the two treatment arms by the difference in mean effectiveness. It will be expressed in cost per QALY gained at 12 months in the CUA and in cost per BMI point gained at 12 months in the CEA. Deterministic and probabilistic sensitivity analyses (bootstrapping methods) will be carried out to assess the uncertainty surrounding the results. Results will be placed on a cost-effectiveness plane and a cost-effectiveness acceptability curve will be constructed to determine the probability that the experimental strategy is cost-effective based on the decision-maker’s willingness-to-pay.

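### Economic evaluation: no adjustment for SF-12 utility at inclusion is named, which costs precision and exposes the QALY difference to chance baseline imbalance

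*Protocol article*

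**What the plan says.** The Economic evaluation section of the protocol article sets two effect measures: "The effectiveness criteria will be quality-adjusted life-years (QALYs) in the CUA and BMI in the CEA". On the first it says "QALY will be derived from patients’ responses to the SF-12 at inclusion, weight normalisation, 6 and 12 months". Table 1 (Measures) confirms that SF-12 is scheduled at inclusion. The incremental ratio is obtained by "dividing the difference in mean costs in the two treatment arms by the difference in mean effectiveness". On uncertainty, "Deterministic and probabilistic sensitivity analyses (bootstrapping methods) will be carried out to assess the uncertainty surrounding the results", and the results feed a cost-effectiveness plane and an acceptability curve.

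No covariate is named for either effect measure. The Statistical analysis plan section does not supply one: for group comparisons of quantitative variables on primary or secondary criteria it lists "Student's t test or non-parametric Wilcoxon test for quantitative variables, according to their normal or non-normal distribution", neither of which adjusts for baseline. The only regression it describes is the one for prognostic factors.

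**The concern.** Inclusion utility enters the QALY twice. It is one of the points that define the area, and it is likely to correlate with the utilities measured later. If one arm happens to start with higher utility, the difference in mean QALYs moves in that arm's favour before treatment has had any effect. With 44 children per arm, such an imbalance need not be negligible.

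The QALY difference is the denominator of the cost-utility ratio. If it is small, noise in it can change its sign, and with it the quadrant of the plane and the course of the acceptability curve. The information needed to remove much of that noise is already collected.

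**Working it through.** **The plan's own figure.** The article gives no design figure for utilities or QALYs. Its only design calculation is for 12-month BMI: margin 1 kg/m², SD 1.35, one-sided 2.5%, 90% power, 40 per group. This reproduces: the exact noncentral t gives power 0.905 at 40 per group (0.898 at 39), and 80 × 1.10 = 88, so 44 per arm. Only the 44 is used below.

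**Assumptions, none of them in the documents.** Utility SD s = 0.12 at every visit (range 0.10-0.15); one common correlation ρ = 0.5 between visits (range 0.3-0.7); weight normalisation at w = 3 to 5 months, the same for all children; QALY as trapezoid area over months 0, w, 6 and 12.

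**Weights.** In years, the visits carry w/24, 0.25, (12 − w)/24 and 0.25. At w = 3 these are 0.125, 0.25, 0.375 and 0.25, with sum 1 and sum of squares 0.28125. At w = 5 they are 0.208, 0.25, 0.292 and 0.25, with sum of squares 0.2535.

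**Formulas.** With a₀ = w/24:
- Slope of QALY on inclusion utility: b = a₀ + ρ(1 − a₀).
- Variance of QALY: V·s², where V = ρ + (1 − ρ)·Σa².
- SE of the unadjusted difference: s·√V·√(2/44), where √(2/44) = 0.2132.
- SE of the adjusted difference: s·√(V − b²)·√(2/44).

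**Worked case, w = 3, ρ = 0.5, s = 0.12.**
- b = 0.125 + 0.5 × 0.875 = 0.5625.
- V = 0.5 + 0.5 × 0.28125 = 0.6406.
- Unadjusted SE = 0.12 × 0.8004 × 0.2132 = 0.0205.
- Adjusted SE = 0.12 × √(0.6406 − 0.3164) × 0.2132 = 0.12 × 0.5694 × 0.2132 = 0.0146.
- Ratio 0.71, a 29% reduction in SE. The variance is about halved, which is the precision of roughly twice as many children.

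**Range at s = 0.12, 44 per arm.**

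| w (months) | ρ | slope b | SE unadjusted | SE adjusted | reduction |
|---|---|---|---|---|---|
| 3 | 0.3 | 0.39 | 0.0180 | 0.0151 | 16% |
| 3 | 0.5 | 0.56 | 0.0205 | 0.0146 | 29% |
| 3 | 0.7 | 0.74 | 0.0227 | 0.0125 | 45% |
| 5 | 0.3 | 0.45 | 0.0177 | 0.0135 | 24% |
| 5 | 0.5 | 0.60 | 0.0203 | 0.0131 | 35% |
| 5 | 0.7 | 0.76 | 0.0225 | 0.0113 | 50% |

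The SEs scale with s; the percentage reductions depend on neither s nor the number per arm.

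**Size of a chance imbalance.** The 95% range at inclusion is ±1.96 × 0.12 × 0.2132 = ±0.05 (±0.04 at s = 0.10, ±0.06 at s = 0.15). An imbalance of 0.05 moves the unadjusted QALY difference by 0.56 × 0.05 = 0.03 (0.39 × 0.05 = 0.02 to 0.76 × 0.05 = 0.04).

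**Simulation check.** In 20,000 simulated trials (w = 3, ρ = 0.5, s = 0.12, 44 per arm, no true effect) both estimators averaged about zero. Their SDs were 0.0204 unadjusted and 0.0147 adjusted. The slope on the observed baseline difference was 0.56 unadjusted and 0.00 adjusted.

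**The case against.** **The formula is only the standard definition of the ratio.** This is correct. The text does not call the difference raw or unadjusted, and an adjusted mean difference would satisfy the sentence equally well. A reader might infer that the plan has deliberately chosen an unadjusted estimator; the article does not support that. An article also condenses a fuller protocol, and a covariate list may stand there. What remains is that the rule, followed as written and read beside the unadjusted tests in the Statistical analysis plan section, leads to the weaker estimate, and nothing shown points to adjustment.

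**Randomisation already protects the comparison.** This also stands. The unadjusted difference is unbiased, and a bootstrap over patients carries chance imbalance into the stated uncertainty. It does not recentre the result, though: the cloud of replicates stays around the observed, shifted difference, and it is wider than it need be.

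**The carry-over is partial.** A reader might take an imbalance to pass one for one into the result. It does not: the direct weight of inclusion utility is only 0.125-0.208 at w = 3 to 5, and with correlation the total is about 0.4-0.8.

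**Every figure is assumed.** True. Inclusion falls in acute undernutrition, so utility then may correlate weakly with later visits. At ρ = 0.1 the same formulas give a reduction of only about 7-14%. The gain shrinks, but under these assumptions it remains a gain.

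**No changed conclusion is shown.** This stands too. The article states no QALY difference of interest and no expectation about QALYs; its non-inferiority margin is for BMI. The acceptability curve also depends on costs, which the authors expect to favour day-patient care.

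**Conclusion.** The point holds as a free improvement to a secondary analysis. The economic evaluation takes the incremental effect as a difference in arm means and names no adjustment for an inclusion utility that is collected and forms part of the QALY. Followed as written, it gives an unbiased but less precise QALY difference that carries about 0.4-0.8 of any chance imbalance at inclusion. Adjustment would cut its SE by roughly 16-50%, and by 29-35% at correlation 0.5. These sizes rest on the assumed SD, correlation, timing and trapezoid area.

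The documents do not support calling the cost-utility result biased or invalid, nor saying that an imbalance would exceed the QALY difference that matters or reverse a conclusion. No size is given for the BMI part, because the article states no correlation between inclusion and 12-month BMI. The primary BMI test and the sample size are not affected.

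**What to change.** Add to the economic analysis plan:
- Estimate incremental QALYs by regression on arm with inclusion SF-12 utility as covariate.
- For the cost-effectiveness analysis, estimate incremental BMI by regression on arm with inclusion BMI as covariate.
- Run these regressions within each bootstrap replicate, so that the ratio, the plane and the acceptability curve all rest on the adjusted effects.
- Report the unadjusted difference as a sensitivity analysis.

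The cost is a sentence or two of text and a few lines of code. Inclusion SF-12 and BMI are both already in Table 1, so no new data and no extra patients are needed. If the full protocol or an economic analysis plan already specifies this, the sponsor need only confirm it.
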